### Compliance

Both groups will have an app installed on a dedicated tablet (the intervention group) or their smartphone (the control group). For the control group, the app does not provide motivational feedback but is solely used to transfer data from the activity tracker to a central research database. To prevent data loss, weekly SMS messages will be sent to both groups with the message "Have you opened your SENS app this week?”. Furthermore, the researchers can verify proper attachment by following the skin temperature evaluated by the sensor via a web module. If the temperature fluctuates over an extended period, a project manager will call the patient to solve potential issues. A standard for adherence to app interventions has yet to be established. However, based on patient feedback, an adherence rate of 70%, meaning that the intervention group will use the app along with motivational feedback for 5 out of 7 weekdays, seems reasonable.

All patients will receive oral and written information on how to attach the sensor, use the app (without a tablet), and use the tablet with motivational feedback. Moreover, all patients will receive a link to a YouTube video presenting the project and providing instructions on how to use the equipment.

### Timing of assessments

Assessment will be performed at baseline (two weeks prior to surgery and randomization), during the intervention (12 weeks post-surgery) (the primary endpoint), and a long-term follow-up on patient-reported outcomes will be performed at 12 months post-surgery (Fig. 2; Flowchart of the study and Table 2: Outcome measurements).

**Fig. 2 Fig2:**
[figure not shown]
Flowchart of the study. Abbreviations: TKA: Total knee arthroplasty; mUKA: Medial uni-compartmental knee arthroplasty; PA: Physical activity; IPAQ: The International Physical Activity Questionnaire; OKS: Oxford Knee Score; EQ-5D-5L: Health-related quality of life; GPE: Global Perceived Effect

**Table 2 Tab2:** Outcome measurement

	**Data Collection ****instrument**	**Collection time**			
		Baseline (2 weeks prior to surgery)	Post surgery (week 1–11)	Post surgery (3 months)	Post surgery (12 months)
**Primary Outcomes**					
Total daily PA (Accelerometer counts)	Accelerometer	X	X	X	
**Secondary outcomes**					
Steps	Accelerometer	X	X	X	
Minutes of physical activity	Accelerometer	X	X	X	
IPAQ	PROM	X		X	X
OKS	PROM	X		X	X
EQ-5D-5L	PROM	X		X	X
Return to work	PROM	X		X	X
GPE	PROM	X		X	X
**Tertiary outcomes**					
Activity types	Accelerometer	X	X	X	
Pain and pain medication	PROM, SMS-survey		X	X	
Adverse events	PROM		X	X	

Patient characteristics (Age, gender, BMI, work type and surgery leg) will be obtained at baseline

*Abbreviations: PA* Physical activit, *IPAQ* The International Physical Activity Questionnaire, *PROM* Patient-reported outcome measures, *OKS* Oxford Knee Score, *EQ-5D-5L* Health-related quality of life, *GPE* Global Perceived Effect

## Outcome measures

### Patient characteristics

At baseline prior to randomization, height and weight will be measured, and gender, age, work type, and surgery leg will be recorded. After randomization (post-surgery), the type of knee arthroplasty (TKA/mUKA) and length of hospital stay will be obtained from patient journals.

### Primary outcome measure

PA will be evaluated by SENS motion® as described above. The primary outcome measure is the between-group change score of total daily PA (accelerometer counts) from baseline to 12 weeks following surgery. Accelerometer counts per day is a cumulative and validated variable based on raw accelerometer data in 3 planes and is a proxy for total daily PA [35].

### Secondary outcome measures

#### Steps

Steps per day are measured with SENS motion® [28, 33].

#### Minutes of physical activity

Minutes of physical activity per day measured with SENS motion®.

#### Self-reported physical activity

Patient-reported PA will be measured by The International Physical Activity Questionnaire Short Form (IPAQ-SF), which is a 7-item questionnaire consisting of open-ended questions surrounding the patient's last seven days' recall of PA [36, 37]. The short and long version of the IPAQ was translated into Danish, and the long version was validated in 2014 [38].

#### The Oxford Knee Score

The Oxford Knee Score (OKS) is a validated 12-item patient-reported questionnaire designed and developed to assess function and pain following TKA [39]. It was translated and validated into Danish in 2009 [40]. The questionnaire generates scores ranging from 0–48, with a score of 48 representing the best outcome post-TKA. Each item response is graded between 0–4.

#### General Health

The EQ-5D-5L is a validated patient-reported questionnaire assessing health-related quality of life and consists of the following dimensions: mobility, self-care, usual activities, pain/discomfort, and anxiety/depression. Each dimension uses a 5-point Likert scale [41]. The EQ-5D-5L has been validated in knee OA patients referred for knee arthroplasty surgery [42].

#### Return to work

At 12 weeks and 12 months follow up, all patients will receive tree questions about changes in work status (retried/sick leave/job-seeking), work type (non-physically demanding/physically demanding), and working time (full-/part-time).

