### Health technology

Health technology, such as wearables and motivational feedback using gamification and nudging principles, are new features within health science. Gamification is traditionally defined as using game mechanics in non-gaming contexts to engage audiences [18] while nudging is a subtle and non-coercive method to influence decisions and behaviors for individual or societal benefit [22]. The use of smartphone apps and wearable devices in monitoring patients’ recovery are on the rise. Constantinescu et al. (2022) [23], in a systematic review, emphasized the potential of the technology to improve rehabilitation and increased self-engagement in TKA patients. However, the review concluded that more research is needed to fully understand the long-term effects and maximise the potential of these technologies. This highlights the need for further exploration into how motivational feedback, through nudging and gamification strategies, can be integrated to sustain physical activity and optimize health outcomes. Incorporating wearables and principles of motivational feedback such as gamification and nudging into health science could catalyze an individualized approach focused on increasing patient motivation for PA with expected improved physical functioning, faster and safer return to work, and increased quality of life. Thus, integrating individual rehabilitation goals into wearables may prioritize a more personalized approach and, thereby, potentially improve the effectiveness of rehabilitation following knee replacement surgery. The use of gamification and nudging has been shown to increase PA in overweight and obese adults [24]. Furthermore, a recent RCT study from Van der Walt et al. (2018) [25], on TKA and THA patients has shown that feedback, only on step counts per day, can play a crucial role in motivating patients to increase their daily PA.

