## Objectives of the studies

This multi-center randomized controlled trial (RCT) nested in a prospective cohort aims to investigate whether PA following knee replacement surgery (TKA or mUKA) can be optimized using an activity monitoring device, including motivational feedback, compared with activity monitoring without feedback (care-as-usual). Furthermore, a prospective cohort will investigate the predictive value of PA level prior to knee replacement for the post-surgical length of stay, return to work, and quality of life.

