### Participants, randomization, and blinding

#### Participants and settings

Patients will be recruited from the Department of Orthopedics and Traumatology, Odense University Hospital, Denmark, and the Department of Orthopedic Surgery, Lillebaelt Hospital, Vejle, Denmark. Prior to inclusion, eligible patients (Table 1; Inclusion and exclusion criteria), will receive verbal and written information about the conditions of the trial and sign a standardized consent form. The longitudinally prospective cohort study includes patients unwilling to participate in the RCT study.

**Table 1 Tab1:** Inclusion and exclusion criteria for patients in the study

Inclusion	Exclusion
Age: 40–85 years	Difficulty adhering to the study protocol
Patients scheduled for primary TKA/mUKA	Refusal of standard care
Understanding both verbal and written Danish language	Known- or newly diagnosed malignancy or palliative care
	Participation in an interventional clinical trial during the last 3 months potentially interacts with the aims of the current study
	Do not own a smartphone
	Undergone surgery using robot-assisted technology (CAS)

*Abbreviations**: **TKA* Total knee arthroplasty, *mUKA* Medial uni-compartmental knee arthroplasty

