### Outcome variables

The primary outcome variable, the between-group change score of total daily PA (accelerometer counts) after 12 weeks, is chosen to examine if short-term PA can be increased with motivational feedback. Furthermore, patient-reported outcome variables are evaluated at 12-month follow-up to evaluate potential long-term effects of the intervention on knee function and quality of life. In addition to the objective PA measurements, patients will respond to a questionnaire regarding their subjective PA. Both approaches are combined to provide a more nuanced understanding of the patients’ PA.

The 12-week follow-up was chosen to identify possible improvements at the end of the acute rehabilitation period, where patients are expected to have returned to an active lifestyle and/or have ended their sick leave. 12 weeks is also a reasonably long timeframe for clinical improvements to occur in patients who have undergone knee-arthroplasty surgery, yet short enough to assume that patients would be able to recall their baseline condition. The 12-month follow-up was selected to capture any potential changes beyond the short-term rehabilitation as an expression of a long-term effect.

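### After surgery, return to work is recorded only as status at 12 weeks and 12 months, so time to return is not measured and the week-12 comparison is weak

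*Protocol article*

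**What the plan says.** The RCT hypothesis in the protocol article lists return to work among the secondary outcomes on which feedback is expected to be superior. The cohort objective is the "predictive value of PA level prior to knee replacement for the post-surgical length of stay, return to work, and quality of life".

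The section Return to work describes the measurement: "At 12 weeks and 12 months follow up, all patients will receive tree questions about changes in work status" (retired, sick leave or job-seeking). The other two questions cover "work type (non-physically demanding/physically demanding), and working time (full-/part-time". None of the three is described as asking when the patient went back or how long sick leave lasted.

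Table 2 has the row "Return to work PROM X X X". The three marks fall under baseline, 3 months and 12 months, and the column for weeks 1–11 is empty. Under Patient characteristics, "gender, age, work type, and surgery leg will be recorded" before randomization. Table 1 sets "Age: 40–85 years" and has no employment criterion.

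On timing, Outcome variables in the Discussion explains that at 12 weeks "patients are expected to have returned to an active lifestyle and/or have ended their sick leave". The Background section Health technology names "faster and safer return to work" among the expected benefits of wearables with motivational feedback.

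**The concern.** Return to work happens on a particular day, and the day carries most of the information. A patient back in week 4 and one back in week 11 give the same answer at week 12. If many patients are back by then, as the choice of week 12 suggests may be so, most of any difference between the arms has closed before the first look. The same applies to whatever pre-surgical activity could predict in the cohort.

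A null result on a named outcome could then mean that feedback does not affect return to work, or that the first look came too late to show it. An analysis plan can choose a model and a denominator, but it cannot recover a date that nobody asked for. This is therefore a point about data collection, and the article gives the trial status as recruiting.

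**Working it through.** **The plan's own figure.** There is none for return to work. The only sample size is for accelerometer counts: 2 × [101,000 × (1.960 + 0.842) / 50,500]² = 62.8, so 63 per group against 62 stated. It reproduces closely but has no bearing on this outcome.

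**Inputs from the article.** 150 patients, 1:1, so 75 per arm; 20% dropout, so 75 × 0.80 = 60 analysed per arm; two-sided α 0.05; about 200 patients in the cohort.

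**Assumptions, not in the article.** 40% of patients in work before surgery, so 60 × 0.40 = 24 workers per arm; exponential time to return; hazard ratio (HR) for return 2.0; 70% or 90% of controls back by week 12.

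**Share back by week 12.** If a share S of controls is still off work, the intervention share still off is S^HR.
- 70% back: 0.30² = 0.09, so 70% vs 91%.
- 90% back: 0.10² = 0.01, so 90% vs 99%.

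**Power from week-12 status**, by exact enumeration of both binomials with n = 24. The lower value is Fisher's exact test, the upper the uncorrected chi-square.
- 70% vs 91%: 36% to 48%.
- 90% vs 99%: 7% to 17%. Only 24 × 0.10 = 2.4 controls and 24 × 0.01 = 0.24 intervention patients are expected to be off work.

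**Power from dates**, log-rank test censored at week 12. With D events, power = Φ(√(D/4) × ln HR − 1.960).
- 70%: D = 24 × (0.70 + 0.91) = 38.6; √9.66 × 0.693 − 1.960 = 0.19; power 58%. Simulation also gives 58%.
- 90%: D = 24 × (0.90 + 0.99) = 45.4; √11.34 × 0.693 − 1.960 = 0.37; power 65%. Simulation gives 63%.

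| Controls back by week 12 | Status | Dates |
|---|---|---|
| 70% | 36–48% | 58% |
| 90% | 7–17% | about 63% |

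**A slower process.** Take medians of 8 and 5 weeks (HR 8/5 = 1.6). Still off at week 12: 0.5^(12/8) = 0.35 vs 0.5^(12/5) = 0.19. With 19, 26 and 34 workers per arm (25%, 35% and 45% of 75, no dropout removed), the chi-square test on status has power of about 21%, 28% and 35%, and the log-rank test about 24%, 30% and 38%. The gain is about 2–4 points.

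**Wider range.** With 15–36 workers per arm (25–60% of 60), HR 1.5–2.0 and 70–95% of controls back, normal-approximation power is 9–62% for status and 16–83% for dates. With 24 workers, HR 1.5 and 90% back it is 16% and 27%. The approximation flatters status when few are off work: it gives 27% for 90% vs 99%, where exact enumeration gives 7–17%.

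**Cohort.** 200 × 0.40 = 80 workers. If 70–90% are back by week 12, 80 × 0.30 = 24 down to 80 × 0.10 = 8 non-returners are left to model. With dates, every return contributes.

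**The case against.** Several stronger readings are tempting, and the article does not support them.

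- **A faster return cannot be detected or predicted.** A reader might infer this, but a faster return still shows in week-12 status as long as some patients are off work: 35% vs 19% in the 8-versus-5-week scenario. Status can also be modelled in the cohort. The comparison is weak, not impossible.
- **Dates would nearly double the power.** In the 8-versus-5-week scenario this appears only if Fisher's exact test on status (13%, 17%, 24%) is set against an asymptotic log-rank test on dates. With like-for-like tests most of the gap goes. The gain is large only when most patients are back by week 12.
- **Retired patients dilute the outcome.** The article says who receives the questions, not who is analysed. There is a retired category and a baseline item, so patients with work to return to may be identifiable. The analysis denominator can be left to an analysis plan, which is not shown.
- **Work is recorded only at 12 weeks and 12 months.** Table 2 marks a baseline item and work type is taken before randomization. The limitation concerns the period after surgery. The Return to work section mentions only the two follow-up times, so it and Table 2 should be reconciled on baseline.
- **The trial hypothesises a faster return.** The hypotheses say return to work. Speed appears only in the Background, and the statement about week 12 is hedged with and/or.

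It is also fair that the main limit is the small number of workers in a trial sized for another outcome, which a date does not change. The full questionnaire is not shown either. What remains is that the article sets out the content and timing of the follow-up questions, and neither yields a time to return.

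**Conclusion.** The point holds as a cheap improvement to a secondary outcome. After surgery, return to work is captured as status, work type and hours at two fixed times, the first chosen partly because sick leave may be over. Time to return is not measured.

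The loss depends on how many patients are back by week 12, which the article does not say. It is a few points of power if return is slow, and most of the power if about 90% of controls are back and the effect is large. These figures rest on an assumed share in work, exponential return and assumed hazard ratios. An HR of 2.0 is favourable: with 90% of controls back it means medians of 3.6 and 1.8 weeks. Even with dates, power stays below 80% in most of the scenarios, so either version is exploratory.

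**What to change.** Add one item to the 12-week questionnaire, or to the weekly SMS already sent: the date of the first day back at work, with part-time and full-time return dated separately. Ask patients already past 12 weeks for the date in the 12-month questionnaire.

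Analyse time from surgery to return, censored at follow-up, in patients whom the baseline item in Table 2 identifies as in work or on sick leave from work. Use the same outcome in the RCT and the cohort, and label it exploratory. State in the Return to work section that the item is also collected at baseline, so that it agrees with Table 2.

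The cost is one extra question and a minor amendment, a smaller stated denominator, and some recall error in patients who give the date late. Power remains low.

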#### Global Perceived Effect (GPE)

At 12 weeks and 12 months follow-up, two GPE questions will be sent to the patient. A 7-point Likert scale using the following answers “Worse," "Slightly worse," “Very slight worse", "The same, "Minimal improvement," "Slightly better," and "Better” will be used to answer the following question: “How do you experience your knee problems now, compared to before the surgery?”.

### Tertiary outcome measures

#### Activity types

Activity types evaluated by SENS motion®, i.e. time spent sleeping/resting, standing, walking, and cycling, will be considered.

#### Pain and pain medication

The patients receive weekly text messages (SMS) with a question about their knee pain the previous week. They will be asked to rate their pain on an NRS scale from 0–10, where 0 corresponds to no pain and 10 corresponds to the worst imaginable pain. Furthermore, patients will receive an SMS with a question about their use of pain medication in the last week. The SMS has four options: i) No use of pain medication the past week, ii) use of non-prescription medicine (e.g., Panodil, Pamol, Ibumetin) at least once during the past week, iii) use of strong painkillers (e.g., Morphine, Tramadol) at least once the past week, and iv) use of both non-prescription medicine and strong painkillers at least once the past week.

### Adverse events

Reporting of adverse events will be elicited through self-reported questionnaires 30 and 90 days after the operation. All events will be coded according to the Medical Dictionary for Regulatory Activities, as currently required by all regulatory authorities, including the US Food and Drug Administration and the European Agency for the Evaluation of Medicinal Products. Additionally, a project staff member will examine the patient's medical record for more severe adverse events 7 and 90 days after TKA/mUKA (e.g. deep vein thrombosis (DVT), lung emboli (LE), death, and re-operation). The motivational intervention for increased PA is non-invasive, and only minor discomfort associated with the procedure is anticipated. In cases of unacceptable pain (NRS > 5) for consecutive days, the project manager can be directly contacted. Patients are informed to follow standard procedures for PA after knee replacement in which it is specified that patients should be aware of signs such as fatigue and pain, which indicate the need to take a break from exercise.

## Discussion

This randomized controlled superiority multi-center trial will evaluate the effect of activity monitoring and motivational feedback following knee arthroplasty surgery. The RCT study is expected to provide high-level evidence of the potential clinical and functional benefits of activity monitoring and motivational feedback after a TKA/mUKA. This trial is a multicenter RCT, which results in increased external validity and generalizability of the results. While the literature demonstrates consistent results on decreased levels of post-surgical PA, there is limited understanding of how to improve post-surgical PA levels and the return to active daily living following knee replacement surgery. Existing studies indicate that many knee patients do not achieve significant improvements after surgery and do not meet World Health Organization recommendations for activity [20]. Consequently, there is a need for interventions that help patients enhance post-surgical physical activity.

### Outcome variables

The primary outcome variable, the between-group change score of total daily PA (accelerometer counts) after 12 weeks, is chosen to examine if short-term PA can be increased with motivational feedback. Furthermore, patient-reported outcome variables are evaluated at 12-month follow-up to evaluate potential long-term effects of the intervention on knee function and quality of life. In addition to the objective PA measurements, patients will respond to a questionnaire regarding their subjective PA. Both approaches are combined to provide a more nuanced understanding of the patients’ PA.

The 12-week follow-up was chosen to identify possible improvements at the end of the acute rehabilitation period, where patients are expected to have returned to an active lifestyle and/or have ended their sick leave. 12 weeks is also a reasonably long timeframe for clinical improvements to occur in patients who have undergone knee-arthroplasty surgery, yet short enough to assume that patients would be able to recall their baseline condition. The 12-month follow-up was selected to capture any potential changes beyond the short-term rehabilitation as an expression of a long-term effect.

### Study design

Prior to this RCT, a qualitative study was conducted including 10 TKA/mUKA-patients. Integrating qualitative research before the RCT strengthens the study design by understanding our population and their perspectives. Furthermore, the qualitative study helped optimize the app for the population and their specific needs. This approach facilitates a more comprehensive and well-informed methodology for conducting rigorous and impactful research.

Only a few exclusion criteria will be employed to improve external validity and generalizability. However, the study may potentially be affected by selection bias. An exclusion criterion of “do not own a smartphone” will be used since the use of a smartphone is necessary for the intervention. Furthermore, the trial is based on patients volunteering for a physical intervention, which can also be a cause of selection bias. The accelerometer used in this trial has a maximum memory capacity of 7–14 days. To prevent data loss resulting from a full memory, it is required to establish a weekly data transfer connection to a smartphone using the dedicated application. Therefore, we decided to send a weekly SMS reminder to patients in the intervention and control groups. This approach may introduce attention bias. Moreover, all patients, whether in the intervention or control group, will be aware of wearing the accelerometer, which also may introduce attention bias. However, using their own smartphones to transfer data should minimize the risk of bias in the control group, resulting in more accurate PA levels for comparison.

Public access to the current protocol paper and prior registration on ClinicalTrials.gov will guarantee transparency regarding the implemented methods and definitions of outcome measures.

